### 3.3. Data analysis

#### 3.3.1. EEG-fNIRS analysis

EEG data will be analyzed with EEGLAB (Delorme and Makeig, 2004) for MATLAB for amplitude power and phase synchrony (Tass et al., 1998). fNIRS data will be analyzed with Satori.^1^

#### 3.3.2. Motion capture analysis

Motion Capture data will be analyzed with the MoCap toolbox (Burger and Toiviainen, 2013) which is a set of functions designed for MATLAB. The movement quantity, to measure changes in mobility, and movement quality on the smooth-jerk axis, to measure changes in rigidity of movement, will be computed (Burger and Toiviainen, 2013; Poikonen et al., 2018; Bryl and Biondo, 2021).

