### 2.5. Modes of delivery

The intervention covers various themes through three different parts (4 weeks per part) with the aim to improve clinical symptoms, physical fitness, cognitive skills and emotion regulations. The intervention was developed by a team consisting of a neuroscientist, a psychiatrist, dance teachers and physiotherapists with previous experience in designing dance and movement interventions for different target groups with internalizing problems (Duberg et al., 2013), functional abdominal pain (Högström et al., 2022) and profound intellectual and multiple disabilities (Lundqvist et al., 2022). The intervention is further described in Table 1. The exercise is partly accompanied by instrumental music and recorded nature sounds and partly made in silence paying attention to one’s own bodily rhythm. The exercise consists of tasks related to cardio and strength training, balance, conscious breathing, body awareness, mental imagery (nature visualizations), flexibility, emotional expression, and movement anticipation together with the facilitator and fellow participants. All the tasks are practiced during a flow of 60-min exercise without any major breaks. To meet the needs of the participants in the group, adjustments and modifications will be presented when necessary. Complexity and physical intensity of the tasks will gradually increase over the 12 weeks intervention periods.

**TABLE 1 T1:** Content of the biweekly 12-week intervention on mixed exercise program with creative movement for adults with schizophrenia.

Minutes	Section	Description	Purpose
		Gathering in a circle	Establishing a feeling of being included
2–4	Body scan	Scanning through the body parts Part 1 (moving), Part 2 (self-massaging and tapping), and Part 3 (moving)	Body awareness Hedlund and Gyllensten, 2010; Ferri et al., 2012; Martin et al., 2016; Gökcen et al., 2020
3–7	Gentle movement, flexibility (warm up/preparation)	Stretching arms, sides, neck, rotating shoulders, back, hip, and knees	Body awareness, increased blood-circulation and synovial fluid, stimulate mental presence. Hedlund and Gyllensten, 2010; Ferri et al., 2012; Martin et al., 2016; Bryl et al., 2020
8–10	Cardio	Reaching, jumping, walking, running	Strengthen cardio-vascular function. Soundy et al., 2014; Firth et al., 2015; Vancampfort et al., 2015b; Cheng et al., 2017
8–10	Choreography	Memorizing a dance sequence	Enjoyment, coordination, body awareness Firth et al., 2017a,b; Chen et al., 2018

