At session 2, 12, and 23 motion capture will be recorded. Those sessions will take place at the movement laboratory. Participants and one instructor will wear small reflex balls on six points: hands, elbows and knees, while doing the training session. Setting up will be done by an engineer at the movement laboratory or the doctoral student. On week 6 of the intervention the same procedure of tests, apart from the accelerometer, cognitive tests and functional brain imaging, will be repeated. After the last session, about two participants and their family members or other next of kin from each group will be purposefully selected for interview. The get a heterogenic group, we will strive for a variation regarding age, gender, participation rate and severity of disease. The participants and their family member or other next of kin will receive written and oral information about the qualitative study (including assurance of voluntariness and confidentiality), before signing a written consent. After finishing the intervention at week 12 all tests from baseline will be repeated in 1–2 weeks. This will also be done after 6 and 12 months, excluding the accelerometer.

The pilot study was conducted in the same way, except there was no control group or randomization procedure nor cognitive or brain imaging measures, nor will there be any follow-up tests in 6 or 12 months.

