**Secondary outcome measures**							
General PANSS and positive symptoms subscale (45 min)	V, O two items			V, O two items		V, O two items	V, O two items
CGI-S and CGI-I (5 min)	V			V, O for CGI-I		V, O for CGI-I	V, O for CGI-I
CDSS (10 min)	V			V		V	V
PSP (10 min)	V			V		V	V
Burden of care, VAS (5 min)	O			O		O	O
BAQ-sv, 10 min	X			X		X	X
EQ-5D-5L, 5 min	X			X		X	X
Weight, length, BMI, 5 min	X			X		X	X
Waistline, 1 min	X			X		X	X
Blood pressure, 10 min rest, 2 min test	X			X		X	X
Resting pulse, 1 min	X			X		X	X
Breathing frequency, 1 min	X			X		X	X
Postural stability/balance, 10 min	X			X		X	X
Chair stand test, 3 min	X			X		X	X
fNIRS-EEG combined with eye tracking during cognitive paradigms including STROOP, verbal fluency, AX-continuous performance test, Emotion regulation test. 45 min	X					X	X
Everyday activity/accelerometer	X (measured at home, 7 days)					X (measured at home, 7 days)	
Motion Capture 60 min		X	X		X		

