#### 3.2.4. Motion capture

Movement of the participants will be recorded with the Qualisys Motion Capture system consisting of 12 cameras (Arqus A12, Qualisys AB, Gothenburg, Sweden) during the movement intervention on sessions 2 on week 1, 12 on week 6 and 23 on week 12. Each participant and the facilitators will have reflective markers attached to the skin on their hands, knees and elbows (six sensors in total per person) which they will wear throughout the movement session. The markers are small and light and will not influence movement.

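### Change in motion-capture measures across sessions 2, 12 and 23 is confounded with the programme's planned progression, so it cannot be read as changed mobility or rigidity

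*Protocol article*

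**What the plan says.** Section 3.3.2 defines two motion-capture endpoints and what each stands for: "The movement quantity, to measure changes in mobility, and movement quality on the smooth-jerk axis, to measure changes in rigidity of movement, will be computed". It names no analysis window. Section 1.5, hypothesis (iii), expects greater mobility and less rigidity than in the control group, and treats motion-capture quantity and fluidity as a way of seeing this.

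On data collection, section 3.2.4 records "during the movement intervention on sessions 2 on week 1, 12 on week 6 and 23 on week 12", with markers "which they will wear throughout the movement session". Section 2.11 says the markers are worn "while doing the training session", and Table 2 lists "Motion Capture 60 min", the same as the session length. Patients and at least one instructor carry markers on the same six points.

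On the tasks being recorded, section 2.5 says: "The intervention covers various themes through three different parts (4 weeks per part". It adds: "Complexity and physical intensity of the tasks will gradually increase over the 12 weeks intervention periods". It also allows adaptation: "To meet the needs of the participants in the group, adjustments and modifications will be presented when necessary".

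**The concern.** A measure of change needs the same task at each occasion, or some way to remove differences between tasks. Here the task is the training itself, and the plan intends the training to become harder and more intense between recordings. A patient whose mobility has not changed, but who follows the programme, would be expected to move more at session 23 than at session 2. Faster or more complex movement may also alter jerk, and could do so in the direction that looks like more rigidity.

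At stake is the reading of one named secondary hypothesis. A rise in quantity could be reported as improved mobility when it shows only that the sessions were delivered as intended. A true reduction in rigidity could be masked, or a false one produced. The primary outcome, PANSS negative symptoms, is not touched.

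**Working it through.** The protocol states no figure for motion capture, so there is none to reproduce. The check has three steps.

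**1. Where the recordings fall.** Inputs: 24 sessions, two per week, three parts of 4 weeks (abstract, section 2.5). Sessions per part = 24 / 3 = 8, so Part 1 is sessions 1–8, Part 2 is 9–16 and Part 3 is 17–24.

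| Recording | Week (session / 2, rounded up) | Part | Position within part |
|---|---|---|---|
| Session 2 | 1 | 1 | 2nd |
| Session 12 | 6 | 2 | 12 − 8 = 4th |
| Session 23 | 12 | 3 | 23 − 16 = 7th |

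Each recording is in a different part. Familiarity with the current part also differs (2nd, 4th and 7th session of the part). Table 2 puts session 2 in week 2 and section 3.2.4 puts it in week 1; it is in Part 1 either way.

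**2. Whether anything holds the task constant.** Sections 2.11, 3.2.4 and 3.3.2 describe no fixed movement test. Section 2.5 states the progression for the tasks in general and exempts none. Section lengths are not fixed either: the lower ends of the Table 1 ranges sum to 2+3+8+8+7+5+4+4+4+2 = 47 min and the upper ends to 4+7+10+10+9+8+6+4+4+4 = 66 min, around a nominal 60. Control participants do not attend these sessions and no control recordings are described, so there is no parallel series from which to subtract the programme's effect.

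**3. What a programme-driven shift would do (illustration).** Assume no true change in the patient, and that the programme alone shifts the measure by k SD of the within-patient change. The value of k is an assumption; the documents give none. For a two-sided paired t-test at 0.05 with n patients, the rejection rate is

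1 − F(t; n−1, k√n) + F(−t; n−1, k√n),

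where F is the noncentral t distribution function and t is the 97.5% point of the central t with n−1 degrees of freedom. I take n = 30 (the intervention arm) and n = 22 (30 × 0.75 = 22.5 after the 25% dropout of section 2.7, rounded down).

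| k | n = 30 | n = 22 |
|---|---|---|
| 0 | 5% | 5% |
| 0.2 | 18.5% | 14.6% |
| 0.4 | 56.3% | 43.3% |
| 0.6 | 88.8% | 76.5% |
| 0.8 | 98.8% | 94.7% |

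The paired test is a simple stand-in for whatever within-group analysis is used.

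**The case against.** Several points on the other side are fair.

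- A reader might infer that the endpoints are computed from whole sessions. The article supports only that whole sessions are recorded. The window could be set in a fuller document. This narrows the point but does not remove it: a later plan can choose a segment, yet it cannot supply an identical task if none was performed.
- A reader might infer that both endpoints improve by design. That is reasonable for quantity. For smooth-jerk nothing in the article shows the direction.
- A reader might take the minute ranges in Table 1 as the size of the progression. The article does not tie the ranges to the parts, and they may simply allow for group needs, so no percentage increase can be drawn from them.
- The sessions share one template. Emotional expression and improvisation are each 4 min, and the body scan is labelled as moving in both Part 1 and Part 3, so it does not separate the first recording from the last. This stands, but a shared template is not an identical task when the tasks are said to progress.
- The instructor's markers already give a reference for task demand. True, and useful, but section 3.3.2 does not say that they will be used this way.
- Lack of control recordings is the larger obstacle to hypothesis (iii), and the discussion already urges caution over secondary outcomes. Both are so. The present problem remains even if the claim is reduced to within-group change.

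**Conclusion.** The point holds in this form: change in movement quantity and smooth-jerk across sessions 2, 12 and 23 is confounded with planned task progression, so neither can be read as changed mobility or rigidity in the way sections 1.5 and 3.3.2 do. Quantity is expected to rise if the programme is followed; the bias in smooth-jerk has no known direction. All three recordings are affected.

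The size cannot be stated from the documents, and the rejection rates above depend entirely on the assumed shift. The conclusion rests on the progression being delivered as section 2.5 describes, and on no fixed movement task existing outside the article. It concerns a secondary outcome, but is worth correcting before the sessions are recorded because it cannot be repaired afterwards.

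**What to change.** In sections 3.2.4 and 3.3.2:

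1. Base both endpoints on one short segment performed identically (same instruction, music and duration) in sessions 2, 12 and 23. The 4-min improvisation block in Table 1 is one candidate.
2. Also report each patient's values relative to the instructor, who wears the same markers in the same session.
3. Treat the remaining session data as a description of delivered intensity.
4. State the result as within-group change only, not as the comparison with control in hypothesis (iii), and note that practice effects remain with a repeated segment.

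The cost is a few sentences and a short fixed script inside three sessions already recorded, with no new equipment or visits. The downside is that less recorded time enters the endpoint.

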#### 3.3.3. Statistical analysis

The InMotion study follows the intention-to-treat paradigm. Complementary analyses will be performed per protocol according to the number of sessions the participant attends. For baseline statistics between the groups, descriptions will be constructed using frequencies and proportions for categorical data and means and standard deviations for continuous variables. Baseline characteristics will be compared using the Fisher exact test for dichotomous outcomes, the Mantel-Haenszel chi-square test for ordered categorical outcomes, and the Mann-Whitney *U*-test or unpaired *t*-test for continuous outcomes. A *P*-value of < 0.05 for the two-tailed test will be considered statistically significant for all outcomes. When deemed necessary, correction for multiple significance will be performed.

The primary outcome analysis will initially be performed using a Fisher exact test to evaluate differences between groups. To analyze the change in scores from baseline between groups for approximately normally distributed variables, a repeated-measures covariance pattern mixed model will be used, adjusting for significant differences at baseline. To identify predictive factors at baseline that might be associated with the primary outcome, a univariable logistic regression analysis followed by a stepwise multiple logistic regression analysis will be performed.

The distribution of continuous variables will be described using the mean and standard deviation or median and interquartile range. Categorical variables will be described with numbers and percentages.

The interviews will be analyzed by qualitative content analysis, to this day planned to be according to Hsieh and Shannon (2005); data from interviews will be transcribed verbatim, read through and analyzed into units. These units will be condensed and coded. The codes will be divided into categories and subcategories, and abstracted to overall themes if found. Latent meaning will be interpreted and the themes shall capture the core message of the whole data-material and will be strengthened with quotes. NVivo software program (QSR International; NVivo, 2022) will be used during the analysis.

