**Methods:**

The study is a mixed-method randomized controlled trial to evaluate the effects of a 12-week intervention for adults with schizophrenia. The treatment group (30 participants) will receive the intervention in addition to standard care and the control group (30 participants) only standard care. The intervention consists of 24 biweekly sessions with a duration of 60 min. The pre-test (weeks from 4 to 2 prior to the intervention) and post-test (week 12) include clinical measure (PANSS), quality of life, social performance, movement quantity, brain function and eye tracking measures. In addition, a treatment subgroup of 12–15 participants and their family member or other next of kin will complete a qualitative interview as a part of their post-test. Two follow-up tests, including clinical, quality of life, brain function and eye tracking will be made at 6 and 12 months from the completion of the intervention to both study groups. The primary outcome is change in negative symptoms. Secondary outcome measures include general and positive symptoms, quality of life, social performance, movement quantity, brain function and eye tracking. Explorative outcome includes patient and family member or other next of kin interview.

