The main study will be a prospective randomized controlled trial (RCT) with 2 parallel groups: an intervention group (30 participants) and a control group (30 participants) of adults with schizophrenia or disorders with symptoms similar to schizophrenia, as described in section “2.3.1. Inclusion criteria.” The intervention consists of sessions on mixed exercise program with creative movement two times a week for 12 weeks in addition to standard medical care as described in section “2.9 Standard care.” Each group will include 4–6 participants under the guidance of two instructors. The control group receives standard medical care and gets access to the video-links after the 12-month follow-up. Most outcomes are measured at baseline, after 6 and 12 weeks, 6 and 12 months (see Figure 1 for details). At all follow-ups, data is collected for both the intervention and control groups. The timeframe of the main study is from autumn 2023 to spring 2025. The study adheres to the standard methodology of intervention research. This protocol is conducted according to the SPIRIT (Standard Protocol Items: Recommendations for Interventional Trials) guidelines (Chan et al., 2013). The study will be reported according to the CONSORT (Consolidated Standards of Reporting Trials) guidelines (Schulz et al., 2010), and COREQ (Consolidated Criteria for Reporting Qualitative Research; Tong et al., 2007).

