### 2.6. Randomization

The participants will be randomly divided into two groups, 30 patients who will receive the mixed exercise program with creative movement intervention in addition to continuing their conventional treatment plan and 30 patients who will only receive their usual treatment. Randomization in the main RCT study will be carried out in sealed envelopes after the baseline measurements. An external statistician will prepare the envelopes that will be delivered to the participants by the research team. Thus, the randomization will be blinded to the research team, meaning the research team will not know the group or identify of the participants when analyzing the data. Due to the nature of intervention studies, blinding toward the participants is not possible. Physical activity cannot be blinded, meaning that the patients know whether they are receiving the treatment or not.

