### 2.13. Frequency and duration

The duration of the biweekly movement intervention will be 60 min, the order and content of which is described in detail in Table 1. Throughout the intervention period, the participants will be encouraged to practice their favorite movement or relaxation techniques at home between the sessions if they want to. Each of the three parts of the intervention will be recorded, and the research team will distribute video-links upon request to the participants if they want to have support in practicing on their own at home. Moreover, when a participant fails to attend a session, an email with the video-link will be sent out, with encouragement to practice at home and keep up the frequency of two sessions a week.

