### 2.15. Adherence

Intervention adherence will be noted by the instructors during both pilot study and main study. To stimulate high adherence to the intervention throughout all the intervention time period, we will work in close collaboration with the clinic, both for reminding about the importance of intervention participation during the 12 weeks and in practical issues regarding getting to the studio in time. To keep the creative physical exercise sessions motivating and interesting, the focus will be on enjoyment, social inclusion and increasing body movement in harmony with music. In addition, the fact that the intervention consists of three different parts with separate themes will hopefully stimulate adherence motivation. To retain as many participants as possible, reminder text-messages and emails will be sent to participants. Notes about participants who discontinue or deviate from the study will be made.

Randomization will minimize bias, but we will assess any change in the treatment plan of the participants including medication, if they stop taking their medication and become ill, or if they change to a better medication and improve because of the intervention.

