In the pilot study, we tested the feasibility of biweekly attendance, which might be challenging for the participants with schizophrenia. However, in the pilot study, there was a high attendance rate and no dropouts. Nonetheless, we are aware that biweekly commitment implies a behavioral change that can be hard to achieve for this target group. Thus, it is interesting to investigate if the format of this intervention can influence motivation, retention, and interest to participate regularly.

The results from this study will broaden the knowledge of the ways non-pharmacological interventions can be valuable for reducing the burden of schizophrenia for patients themselves, their families, and the healthcare system. Mixed physical exercise with creative movement could be an example of an easy-access joyful intervention as a complementary treatment.

To conclude, this randomized controlled study with 60 participants will investigate the effects of combined physical, creative and social training in adults with schizophrenia. The primary aim is to study the effects of the intervention on negative symptoms of schizophrenia, but several other aspects, such as physical skills and health-status, cognitive and emotional capacity and brain functions related to them as well as movement quantity and mimicry, will also be studied. The results from this intervention study may provide useful information and potentially a complementary treatment to use for caregivers in primary healthcare and psychiatric in- and outpatient clinics.

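### Defining the supportive per-protocol analysis by sessions attended selects within one arm only, so its result can be biased in either direction

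*Protocol article*

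**What the plan says.** Section 3.3.3 states the main principle first: "The InMotion study follows the intention-to-treat paradigm". The next sentence adds the supportive analysis: "Complementary analyses will be performed per protocol according to the number of sessions the participant attends". It names no comparator.

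The rest of the article settles who can have an attendance count:

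- The abstract gives the maximum: "The intervention consists of 24 biweekly sessions with a duration of 60 min".
- Section 2.6 describes the other arm as "30 patients who will only receive their usual treatment".
- Section 2.2 confirms that controls have no route to the programme during the trial: "The control group receives standard medical care and gets access to the video-links after the 12-month follow-up".
- Attendance is logged on the intervention side (section 2.15): "Intervention adherence will be noted by the instructors during both pilot study and main study".

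Two further statements bear on what attendance means. Section 2.13 says that "when a participant fails to attend a session, an email with the video-link will be sent out, with encouragement to practice at home". The Discussion concedes that "we are aware that biweekly commitment implies a behavioral change that can be hard to achieve for this target group".

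**The concern.** Attendance is decided after randomisation, by the participant, and can be observed in one arm only. A rule based on it can remove people from the intervention arm but has nothing to act on among controls. A session cut-off written into a later analysis plan would not cure this, because the difficulty lies in the selection variable and not in where the line is drawn.

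The article gives reasons to expect a link between attendance and outcome. The primary outcome is the PANSS negative subscale. Section 1.2 counts asociality and reduced mobility among negative symptoms, and section 1.4 notes low motivation for physical activity in this population. Section 2.15 foresees participants who stop medication and become ill, an event that could both reduce attendance and worsen PANSS. The stated covariate adjustment is for significant differences at baseline, which does not reach such post-randomisation events.

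The session count is also an imperfect measure of exposure, because absentees are sent the video and urged to practise at home.

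The stake is interpretive. In a trial of 60, a null intention-to-treat result beside a significant result in attenders could be taken to show that the programme works for those who take part.

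**Working it through.** The article gives no figure for the per-protocol analysis, so there is none to reproduce. The check asks how far attendance-based selection could mislead when the intervention has no effect.

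**Inputs from the article:** 30 per arm (section 2.7) and two-sided 0.05 (section 3.3.3).

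**Assumed inputs:** the share f of the intervention arm kept, the correlation rho between attendance and outcome, and, in case B, a baseline-to-follow-up correlation of 0.6. The article gives none of these, so f and rho are shown as ranges.

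**Case A: attendance follows the post-baseline course, and attenders are compared with all controls.** Under normality the spurious benefit in SD units is

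bias = rho × φ(z) / f, where z is the standard normal point with upper tail f.

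The factor φ(z)/f is 0.399/0.50 = 0.798 for f = 0.50, 0.348/0.70 = 0.497 for f = 0.70, and 0.280/0.80 = 0.350 for f = 0.80. With rho = 0.3:

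- f = 0.50: 0.3 × 0.798 = 0.24 SD
- f = 0.70: 0.3 × 0.497 = 0.15 SD
- f = 0.80: 0.3 × 0.350 = 0.10 SD

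For the type I error, 40,000 null trials per setting were simulated. The best-attending 15, 21 or 24 of 30 were compared with all 30 controls by a t-test:

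| Share kept | rho 0.2 | rho 0.3 | rho 0.5 |
|---|---|---|---|
| 0.80 | 5.8% | 6.7% | 9.8% |
| 0.70 | 6.2% | 8.2% | 13.8% |
| 0.50 | 7.8% | 11.0% | 23.7% |

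With rho = 0 the error stays at about 5%. The intention-to-treat comparison stays at 4.8–5.2% in every setting. When rho is positive, nearly all the excess rejections favour the intervention. With 22 per arm, roughly what remains after the planned 25% dropout (30 × 0.75 = 22.5), the figures at rho = 0.3 are lower: 9.4% at f = 0.50 and 6.0% at f = 0.80.

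**Case B: attendance follows baseline severity only, and the outcome is change from baseline.** Attenders then start milder by m = rho × φ(z)/f, where rho is now the attendance–baseline correlation. At follow-up they are expected to be milder by only 0.6m. Their reduction is therefore smaller than that of controls by m − 0.6m = 0.4m:

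- rho = 0.3, f = 0.70: 0.4 × 0.149 = 0.06 SD against the intervention
- rho = 0.5, f = 0.50: 0.4 × 0.399 = 0.16 SD against the intervention

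In simulation over rho 0.3–0.5 and f 0.50–0.70, false rejections in favour of the intervention fall to 0.6–1.4%, below the nominal 2.5% for that side.

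**Within-arm reading.** If the sentence means a dose-response by session count among intervention participants, controls play no part. The same correlation between attendance and prognosis then appears directly as an apparent dose effect.

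**The case against.** The strongest reply has four parts.

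1. **The comparator is inferred.** The sentence does not say that attenders are set against all controls, and it also fits a within-arm dose-response. This stands, so the point is put conditionally. Neither reading escapes self-selection.

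2. **The direction is not fixed.** A reader might infer that the analysis must favour the intervention. The article does not support that. Its outcome is change in negative symptoms, and case B shows the bias reversing if attendance tracks baseline severity. This stands in full.

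3. **The consequence is limited.** Intention-to-treat governs and the attendance analysis is called complementary. A reader might infer that the trial's randomised comparison is lost or that its conclusions will rest on attenders. Nothing in the article says so. The size also depends on assumed inputs and is small with high attendance or a weak link. This stands, and it confines the point to the supportive result.

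4. **Details belong to an analysis plan.** A cut-off, the definition of the analysis set and the adjustment method may well sit in a document not shown, and their absence is not criticised here. What the article does fix is the selection variable, and that is the source of the problem.

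A complier-average estimate has its own weakness: home video practice by people counted as non-compliers strains the assumption that they were unaffected. That is a fair criticism, and the fix takes account of it.

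**Conclusion.** The point holds in a limited form. A per-protocol analysis defined by sessions attended can select only within the intervention arm, and either reading of it is open to bias from self-selection. If attendance follows the post-baseline course, then with no true effect, an assumed correlation of 0.3 and 50–80% of the arm kept, the spurious benefit is about 0.10–0.24 SD and the type I error about 7–11%. It stays near 5% at high attendance or weak correlation. If attendance follows baseline severity, the bias on a change score is about 0.06–0.16 SD against the intervention, assuming a baseline-to-follow-up correlation of 0.6, attendance correlations of 0.3–0.5 and 50–70% kept. The intention-to-treat analysis is unaffected. The change is worth making because it is cheap and concerns a result that readers will see beside the main one.

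**What to change.** Keep all efficacy conclusions on intention-to-treat. Replace the between-group per-protocol comparison with a complier-average causal effect that uses randomised arm as the instrument. Controls have no access to sessions or videos until after the 12-month follow-up, so non-compliance is one-sided by design and the attendance log already kept is enough.

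Because absentees are sent the video, define compliance by a low threshold (for example, any session attended) or as the number of sessions. State the assumption that video use below the threshold has no effect. If session count is used, say that home practice is not in the count. Report attendance against outcome within the intervention arm as descriptive only.

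The cost is a sentence or two in the plan and one extra model, plus the exclusion assumption and a wider interval. In the simplest form the estimate and its standard error are roughly the intention-to-treat values divided by the compliance share. With 30 per arm, unit SD and an illustrative share of 0.7, the standard error is √(2/30)/0.7 = 0.258/0.7 = 0.37. The naive comparison of 21 attenders with 30 controls has √(1/21 + 1/30) = 0.28. A lower threshold raises the share and narrows the gap. The estimate adds little evidence beyond intention-to-treat; its use is to describe the effect of taking part without giving up the randomised comparison.
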